## Abstract

**Background:**

For many people living with and beyond cancer (LWBC), physical activity (PA) declines significantly after supervised PA interventions. The effect of short-term, supervised PA interventions on motivational outcomes and longer-term PA in people LWBC is limited, especially theoretically-based approaches to identify key motivational outcomes for behavior change. The purpose of this study is to compare the effects of a 6-month virtual supervised PA group plus standard exercise counseling (PA + EC) versus a virtual supervised PA plus motivationally-enhanced behavioral counseling (PA + BC) group on moderate-to-vigorous intensity PA (MVPA) in people LWBC.

**Methods:**

This study is a two-armed, multi-site randomized controlled trial (RCT). People LWBC will be recruited and randomized to a 6-month virtual supervised PA intervention plus standard exercise counseling (PA + EC group; *n* = 118) or a 6-month virtual supervised PA plus behavioral counseling based on the Multi-Process Action Control (M-PAC) framework (PA + BC group; *n* = 118). Supervised PA will be delivered via synchronous Zoom classes that tapers to a home-based protocol at the end of the study. The goal of both groups is to gradually increase PA to the cancer PA guidelines (e.g., 90 min of MVPA/week). The PA + BC group will receive twelve behavioral counseling sessions with a qualified exercise professional (QEP), and the corresponding counseling session will be delivered bi-weekly. The behavioral counseling sessions will be based on the M-PAC’s reflective, regulatory, and reflexive processes. In addition to the supervised PA classes, the PA + EC (i.e., attention control group) will receive twelve standard PA counseling sessions based on PA training principles. People LWBC will complete measures at baseline, midpoint, post-intervention (6-months), at 6-months follow-up, and 1-year follow-up. Self-reported measures include quality of life (QoL), motivational outcomes, health economics, and patient satisfaction. Objective measures include PA via accelerometry. Multilevel modelling will examine change in the primary (i.e., PA) and secondary outcomes (i.e., motivational outcomes from the M-PAC, physical function, QoL) at the five time points.

**Discussion:**

This study will create greater understanding on efficacious programming to support PA maintenance that can be used by clinical and community-based organizations as a low-cost, supportive care tool to improve health outcomes for people LWBC.

**Trial registration:**

Clinicaltrials.gov ID NCT06624930.

## Background

Many people living with and beyond cancer (LWBC) suffer from long-term side effects, such as fatigue, depression, and muscle loss, which contribute to poor quality of life (QoL) [1–4]. Physical activity (PA) has a positive impact on clinical outcomes including improvements in overall QoL, reducing treatment-related toxicities and cancer-specific mortality [3, 5]. Despite these benefits, the majority of people LWBC are not meeting PA guidelines [6–8]. People LWBC are realizing that they can receive quality and engaging access to care that are live remote (i.e., real-time feedback) to self-manage their symptoms [9]. This represents a unique opportunity to test and deliver live remote PA interventions in both clinical supportive cancer care and research trials [10]. Short-term supervised PA programs can improve fitness and participant-reported outcomes in people LWBC [1–4], but PA declines significantly post-intervention and long-term adherence is often low [11–14]. To achieve long-term health benefits, behavior change must be sustained [15]. 

Recent cancer specific PA guidelines for people LWBC suggest a minimum of 90 min of moderate-to-vigorous intensity PA (MVPA) per week, and at least 2 days of large muscle strength training per week [8] to improve side effects of cancer treatment benefits [8, 16]. However, 74.8% and 86.1% of people LWBC are not currently meeting aerobic PA and combined PA guidelines (i.e., 150 min of MVPA/week and/or 2 days/week of resistance training), respectively [7]. Given that people LWBC face several barriers to engaging in in-person PA (e.g., distance from clinical/community programs, treatment-related side effects [17], there is a need to develop and assess the efficacy of live remote approaches [18, 19]. The quality and effectiveness of live remote interventions relative to non-telehealth home-based exercise or rehabilitation interventions are still unclear [20–22]. Theoretical approaches to identifying key motivational outcomes to facilitate the adoption and maintenance of PA are limited [15, 23–25]. Behavior change techniques such as self-monitoring, goal setting, social support, and action planning are shown to be effective techniques and produced the largest overall effect size for behavior change in people LWBC [14]. Behavior change interventions are complex with numerous interacting components that are often poorly described, especially with regard to how maintenance is defined [26]. This hinders the understanding of intervention components that might facilitate PA maintenance [15]. Behavior change interventions improve PA over the course of the intervention; however, PA declines are more pronounced as the length of time between follow-up assessments increase [27]. Nevertheless, the inclusion of theoretical components increases the likelihood of behavior change in these interventions [15, 28]. 

The dominant theoretical approach in PA and cancer survivorship studies are social cognitive theories [23, 24, 29]. While informative, these theories rarely focus on maintenance through enacting on intention-behavior gap mechanisms [30]. The Multi-Process Action Control (M-PAC) framework [30] has a causal structure where an individual moves from intention formation to adoption of action control and onto maintenance of action control. According to the M-PAC [30], *reflective processes* (i.e., instrumental attitudes [expected benefits from performing PA], affective judgements [expected pleasure from performing PA], perceived capability [one’s ability to perform PA] and perceived opportunity [perceived social/environmental circumstances to perform PA) are necessary for PA intention formation in people LWBC. When these expectations are strong and positive, they culminate in the formation of PA intention (i.e., decision to enact regular PA). The dominant determinant when beginning regular PA is marked by the enactment of regulatory processes. *Regulatory processes* represent the behavioral, cognitive, and affective regulation strategies (e.g., planning, monitoring, attention focus, emotion regulation) that are enacted to translate intention into PA. Finally, *reflexive processes* comprised of habit [learned cue-behavior associations] and identity [role self-categorization] are those constructs that develop as a consequence of repeated successful behavioral outcomes over time. Taken together, behavior change is the product of reflective, regulatory, and reflexive processes that have facilitated an initial intention into successful on-going behavior [30], including people LWBC [31–34].

Motivating people LWBC to be physically active requires behavioral skills training and understanding the behavioral mechanisms for change which our study addresses. In a critical narrative review [26], 20 theories and conceptual papers on PA maintenance were identified with the social cognitive (e.g., Social Cognitive Theory), humanistic (i.e., Self-determination Theory), and socioecological approaches (i.e., Ecological Model of Physical Activity) which have left maintenance undifferentiated from initiation. Kwasnicka et al.’s [35] review identified five themes (e.g., maintenance motives, self-regulation, habits) that may need to be considered for maintenance, and the associated constructs within these themes (e.g., dual process models and habits, identity). The M-PAC includes all of these themes outlined above and is predicated on multiple lines of behavioral research in PA [26]. Thus, there is strong empirical evidence for M-PAC in both behavioral prediction and change in general populations and people LWBC [27, 36, 37]. There is considerable evidence (> 40 studies) for the M-PAC structure and constructs in terms of predictive validity, as well as sensitivity of change of these measures in randomized controlled trials (RCT) [28, 30, 37, 38] in people LWBC [31–34]. Specifically, a pilot study demonstrated the feasibility of delivering the M-PAC constructs in prostate cancer survivors over 12 weeks [32]. The behavioral counseling sessions were based on the M-PAC, and included behavior change techniques such as social support, goal setting, self-monitoring, action planning, habit, and identity. The behavioral counseling group increased MVPA by 24 min more than the exercise counseling group did. Preliminary evidence suggests that adding behavioral counseling to supervised PA in people LWBC may be feasible and result in better adherence to PA compared to exercise counseling alone, although this needs to be replicated in larger trials with sufficient follow-up period (i.e., ≥ 6 months) for PA maintenance. The addition of reflexive processes (habit, identity) [26, 35], which have received less attention, may be critical constructs that explain PA maintenance [39–42]. Furthermore, factors influencing PA adherence and maintenance have largely ignored sex and gender differences (i.e., socially manufactured roles, behaviors, expressions, identities) [43]. 

Therefore, the primary purpose of this study is to compare the effects of delivering an entirely virtual 6-month supervised MVPA group plus standard exercise counseling (PA + EC) versus a virtual supervised MVPA plus motivationally-enhanced behavioral counseling (PA + BC) group on MVPA in people LWBC. We hypothesize that the PA + BC group will increase MVPA compared to the PA + EC group at mid-intervention (T1; 3 months), post-intervention (T2; 6 months), 6-month follow-up (T3; 6 months post-intervention), and 1-year follow-up (T4; 1-year follow-up from post-intervention). Secondary outcomes include: (1) to determine the effects and cost-effectiveness of PA + EC versus PA + BC on secondary outcomes, including changes in reflective, regulatory, and reflexive processes from the M-PAC, physical function, QoL and costs; (2) to examine the regulatory and reflexive mediators of the 6-month intervention on MVPA; and (3) to examine moderators of treatment efficacy in the PA intervention. We will compare across various demographics (e.g., intersection of age, sex, gender, ethnicity, body mass index), fitness (e.g., baseline PA), and clinical subgroups (e.g., cancer type), as well as adherence and intervention completion across groups. This study will address gaps in the PA maintenance literature to demonstrate: (1) changes in absolute values across behavioral performance of people LWBC, (2) an increase in their magnitude of effect on PA over time; [26] and (3) sex and gender differences in PA maintenance.

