### Recruitment procedures

#### Participant eligibility

Eligibility for this study include those who are: 1) ≥ 18 years of age, 2) have a confirmed diagnosis of cancer of any type (Stages I to III; localized), 3) have completed primary cancer treatments within 5 years, 4) at least 12 weeks post-surgery and/or 6 weeks post-radiation, 5) are proficient in English, 6) are physically inactive (self-report < 90 min of MVPA/week) [45], 7) ambulate in daily life with minimal gait aid use (i.e., aid versus no aid), 8) have access to and can operate a smartphone/tablet/computer with a webcam for videoconferencing and a Bluetooth connection, 9) have access to the internet, and 10) have no cardiac contraindications (e.g., unstable angina, heart failure, coronary artery disease, diagnosed abnormality of heart rhythm). Participants are excluded if they: (1) have a medical condition that prohibits PA (e.g., joint restriction or weight bearing precautions), (2) have uncontrolled comorbidities or cardiovascular contraindications that would increase risk associated with supervised and unsupervised PA (e.g., cardiac contraindications, severe arthritis, recent fall within last 6–12 months), (3) advanced cancer (i.e., Stage IV; metastatic), and (4) do not intend to live in Canada for the next 18 months.

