*Quality of Life -* QoL will be assessed by the validated Functional Assessment of Cancer Therapy-General (FACT-G) which consists of physical well-being (PWB), functional well-being (FWB), emotional well-being (EWB), and social well-being (SWB) [64]. The FACT-Fatigue (FACT-F) scale includes the 27 items from the FACT-G scale plus the 13-item fatigue subscale, which is our primary QoL outcomes [64, 65]. Test-retest reliability is 0.92 for the total scale and 0.82–0.88 for subscales [64]. QoL will also be assessed with the EuroQol-5D (Eq. 5D) [66] as a part of the evaluation of cost-effectiveness.

*Demographic*,* Gender*,* Medical Information and Participant Satisfaction -* Demographic variables include: age, sex, gender, marital status, highest level of education, current employment status, ethnicity, PA history, and body mass index. Medical variables include: cancer type, time since diagnosis, disease stage, current/prior treatments, previous recurrence, current disease status, and comorbidities [67, 72]. Participant satisfaction items will assess burden and overall impressions similar to our prior work in people LWBC [32, 49]. We will disaggregate and analyze all primary and secondary outcomes by gender and sex [68]. 

Other demographic (e.g., age, ethnicity) and clinical (e.g., time since treatment) variables that intersect with gender will also be considered. The approach recommended by experts in gender-related measures is the two-step approach (Centre of Excellence for Transgender Health), which involves asking participants about both their current gender identity and their sex assigned at birth [69]. The Gender Index [70–72] will be used which includes all four aspects of gender (e.g., gender roles, gender relations, institutionalized gender, gender identity). Specific M-PAC constructs (e.g., perceived capability, habit, identity) may vary by sex and gender, thus targeting these considerations may maximize the potential effectiveness of PA interventions [41, 73]. This will prompt gender-specific, patient-centric care pathways for PA interventions designed to maximize the effectiveness of PA and patient outcomes.

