#### Statistical analysis

A series of multilevel models using full information maximum likelihood to examine changes in the primary (i.e., MVPA) and secondary outcomes (i.e., reflective, regulatory, and reflexive processes from the M-PAC, physical function, QoL) will be conducted at the four time points. Multilevel modelling allows for simultaneous assessments of within person variations at each time measurement (level 1), which will be nested within study group (level 2). Finally, study group will be nested within study site (level 3). Although our primary time point of T2 will confirm the adherence reported post-intervention, inclusion of the T3 and T4 assessments allows us to determine if adherence is maintained. Fixed effects included in models will be time (i.e., baseline, T1, T2, T3, and T4), group (i.e., PA + BC intervention and PA + EC attention control), and interaction. All models will be estimated while adjusting for covariates (e.g., baseline PA, age, sex, treatment and cancer type). We will use the same analytical approach to assess differences across subgroups (e.g., sex, gender, drop-outs) by modeling the changes over time. Differences between men and women will be analyzed by adding a gender indicator variable to each of the models. The gender covariate will be crossed with the model’s independent variable so their interaction will be in the model. An intention-to-treat analysis will be used. For missing data at post-intervention or follow-up, all available data will be included under the missing-at-random assumption of the mixed-model analysis. Additionally, sensitivity analyses will be conducted to evaluate the robustness of our findings under alternative missing data assumptions, such as not-missing-at-random. The PROCESS macro for SPSS [77] will be used to examine mediation effects of the reflective, regulatory, and reflexive processes between groups (PA + BC group; PA + EC group) and MVPA and indirect effects across the path model. Cost and QALY differences between groups will be calculated using ordinary least squares regression analyses. Incremental cost-effectiveness ratios (ICER) will be calculated by dividing the adjusted incremental costs by incremental effects. ICER uncertainty will be measured by bootstrapping using at least 5000 replications.

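### The gender moderation model carries cancer type only as an adjusting covariate, so a treatment effect that differs between sex-specific cancers, if there is one, could be misread as a sex or gender difference

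*Protocol article*

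**What the plan says.** The last sentence of the Background promises to demonstrate "sex and gender differences in PA maintenance". The Secondary outcomes section adds that this work will lead to care pathways specific to gender.

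Under Participant eligibility, participants must "have a confirmed diagnosis of cancer of any type (Stages I to III; localized"; no quota by cancer type is given. Randomization is stratified by prior chemotherapy, age and sex, not by cancer type.

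Cancer type appears in two places that matter here:

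- Statistical analysis: "All models will be estimated while adjusting for covariates (e.g., baseline PA, age, sex, treatment and cancer type".
- Background: after the aim "to examine moderators of treatment efficacy in the PA intervention", the comparisons listed include "clinical subgroups (e.g., cancer type), as well as adherence and intervention completion across groups".

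The Statistical analysis section says of subgroups: "We will use the same analytical approach to assess differences across subgroups (e.g., sex, gender, drop-outs) by modeling the changes over time". Of gender it says: "The gender covariate will be crossed with the model’s independent variable so their interaction will be in the model". The Secondary outcomes section says that "clinical (e.g., time since treatment) variables that intersect with gender will also be considered", without giving a model.

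**The concern.** Some cancers occur wholly or almost wholly in one sex. With any cancer eligible, sex and gender will be partly tied to cancer type and its treatment. Stratifying by sex and recruiting the sexes equally do not loosen that tie, because it exists within each arm.

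A main effect for cancer type removes differences in the level of MVPA between cancers. It does not remove a difference in treatment effect between cancers. When gender-by-group is in the model and cancer-type-by-group is not, the gender term takes up that difference.

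What is at stake is interpretation. A care pathway built around gender presumes that gender carries the difference. If the type of cancer carries it, the pathway is aimed at the wrong characteristic. The primary comparison of the two arms is not affected.

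**Working it through.** **Scale.** The plan's only relevant figure is 196 analysable participants for 80% power at alpha 0.05 to detect 24 min per day of MVPA (Sample size). No SD is given, so the figure cannot be reproduced, only solved backwards. Assuming a two-sided test with 98 per arm:

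- implied standardized effect = (1.960 + 0.842) × √(2/98) = 0.400
- implied SD = 24 / 0.400 = about 60 min per day

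**What the gender term picks up.** Let s be the share of each sex with a sex-specific cancer, e the treatment effect in that cancer, and eC the effect in cancers that both sexes share. With no true sex effect, the apparent difference in treatment effect, women minus men, is

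sF(eF − eC) − sM(eM − eC).

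It is zero when effects do not vary by cancer. It is also zero when the two products are equal.

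**Prostate-only scenario (assumed).** Set eF = eC, let 40 to 60% of men have prostate cancer, and let the effect there be 0.2 to 0.5 SD larger.

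- Size of the apparent interaction: 0.4 × 0.2 = 0.08 SD to 0.6 × 0.5 = 0.30 SD.
- SE of the main comparison: 2/√196 = 0.143 SD. SE of the interaction with equal sexes: 2 × 0.143 = 0.286 SD.
- Two-sided rejection at 0.05: 5.9% at 0.08 SD and 18.3% at 0.30 SD.

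**Simulation check.** Linear models of MVPA change at one time point, N = 196, half women, SD 60, 3,000 runs per scenario, no true sex effect, eC = 24 min. Both sexes have the same sex-specific share. Interaction and SE are in minutes.

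| Share | eF, eM (min) | Cancer type as main effect: mean interaction; rejection | With separate male- and female-specific cancer × group terms: rejection | SE of sex × group, before → after |
|---|---|---|---|---|
| 30% | 12, 36 | −7.0; 7% | 5% | 17 → 21 |
| 50% | 12, 36 | −11.7; 11% | 5% | 17 → 24 |
| 80% | 12, 36 | −19.6; 20% | 5% | 17 → 40 |
| 30% | 0, 48 | −14.5; 13% | 4% | 17 → 21 |
| 50% | 0, 48 | −23.3; 27% | 5% | 17 → 24 |
| 80% | 0, 48 | −38.8; 59% | 5% | 17 → 40 |

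With equal effects in all cancers (24, 24, 24), rejection under the main-effect model was about 5% at every share.

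**Which added term works.** One pooled indicator (sex-specific or not) crossed with group does not work. The fitted sex term is then an average of the sex differences within the two cancer classes, each weighted by nM·nF/(nM + nF). Take a prostate effect 0.5 SD larger and no other shift.

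- 50% sex-specific in each sex: the weights are equal, so the term is 0.5 × 0.5 = 0.25 SD, the same as without it.
- 50% of men and 80% of women: the weights are 0.5 × 0.8/1.3 = 0.308 (sex-specific) and 0.5 × 0.2/0.7 = 0.143 (shared). The term is 0.5 × 0.308/0.451 = 0.34 SD, worse than 0.25.

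Separate male-specific and female-specific terms, or restriction to shared cancers, remove it.

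**The case against.** Four points stand against a stronger reading.

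1. A reader might infer that cancer type enters the whole plan only as a main effect. The document does not support that: the Background sets a moderator aim and names cancer type as a clinical subgroup, and the subgroup list in the Statistical analysis section is open-ended. The limitation is confined to the gender model. A separate cancer-type analysis would not cure it, since two one-factor analyses can both show the same difference without saying which factor carries it.
2. A reader might infer that a false sex or gender difference will be reported. That needs real variation in effect by cancer, and the document gives no evidence of it. The Randomization section allows that treatment characteristics may affect response, and the pilot behind the 24 min was in prostate cancer survivors. These make variation conceivable, no more. The shares and shifts above are assumptions; the largest shift (0.5 SD) exceeds the implied 0.40 SD effect, and the prostate-only case sets the female-specific shift to zero.
3. The full-sample contrast is still a valid description of the men and women enrolled. Only its attribution is in doubt.
4. Which interaction terms share a model is often settled in an analysis plan, which is not at hand, and the Secondary outcomes section does say that clinical variables intersecting with gender will be considered. That is fair, but the article does state a gender model, and as stated it cannot separate the two explanations.

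**Conclusion.** The point holds in a limited form. As described, the gender model does not separate moderation by gender from moderation by cancer type, and nothing else in the article joins the two. If effects differ between sex-specific cancers, the gender-by-group term could be misread.

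The size is unknown: zero with no variation by cancer or with cancelling shifts, and 0.08 to 0.30 SD in the prostate-only scenario, with false-positive rates of about 6 to 18%. It rises to 59% only in the most extreme simulated case. All of this rests on assumed shares and effects and, for the minutes, on an SD solved backwards from the sample size. This is a cheap improvement to a secondary claim, not a flaw in the primary analysis.

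**What to change.** Repeat the sex and gender by group (by time) contrast in participants whose cancers occur in both sexes, and report it beside the full-sample contrast. Equivalently, add separate male-specific and female-specific cancer × group (× time) terms to the gender model; do not use one pooled term. Fix the list of cancers counted as sex-specific before the data are analysed.

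Describe the full-sample contrast as a difference between the men and women enrolled. Attribute it to sex or gender only as far as the restricted estimate and its interval support that.

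No new data are needed, since cancer type is already collected. The cost is precision: in the simulations the SE of the interaction rises from about 17 min to 21, 24 or 40 min when 30, 50 or 80% of each sex has a sex-specific cancer. The Sample size section asserts enough power for sex and gender analyses without a calculation, so the result should be presented as exploratory.
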